### Endpoints

The primary endpoint is the cumulative rate of toxicity CTCAE ≥ grade 2 in the first 4 months. Secondary endpoints are progression-free survival (secondary endpoint of special interest), overall survival, acute and late toxicity, quality of life and neurocognition.

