### Statistical considerations

The primary study objective is to demonstrate that the toxicity rate (rate of CTCAE toxicity grade ≥ 2) under proton therapy, π^Pr^, is lower than the toxicity rate under photon therapy, π^Ph^. Thus, the null hypothesis of the study is that the toxicity rate in the proton group is greater than or equal to the toxicity rate in the photon group, i.e., H_0_: $${\pi }_{A}^{Pr}\ge {\pi }_{A}^{Ph}$$. For sample size planning, rates of $${\pi }_{A}^{Ph}=21\%$$ for the photon group and $${\pi }_{A}^{Pr}=9\%$$ for the proton group were assumed under the alternative hypothesis. This assumption results from a matched-pair analysis of the Heidelberg patient collective [6]. Under these assumptions, 276 evaluable patients (138 per group) are needed to reject the null hypothesis with a power of 1-β = 80% using the chi-square test at the one-sided significance level α = 0.025. Assuming a dropout rate of 15%, 326 patients (163 per group) will be included in the study. In the analysis, a logistic regression model will be applied for the evaluation of the primary endpoint adjusting for the confounders "fractionation," "subventricular zone involvement", and "concurrent chemotherapy". It is expected that this will increase power as compared to using the chi-square test. The secondary variables will be evaluated with methods of descriptive data analysis.

The intention-to-treat (ITT) population is the primary evaluation population for all efficacy endpoints and patient characteristics. The ITT population comprises all randomized patients which are evaluated in the treatment arm to which they were randomized. The per-protocol (PP) population includes all patients in the ITT population who received the planned therapy in its entirety and for whom documentation is complete with respect to the primary endpoint. The analyses of the PP population serve as sensitivity analyses, which will be used to investigate the robustness of the results from the ITT analysis. All patients in the ITT population in whom the planned therapy was started (at least 1 day) belong to the safety population and will be evaluated in the therapy arm to which they were treated. This is the primary evaluation population for the primary endpoint as well as for all other safety endpoints.

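### The trial's only confirmatory test, lower toxicity with protons, is run in an as-treated safety population and no analysis by randomised arm is made primary

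*Protocol article*

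**What the plan says.** All of this is in the Protocol article. Under Endpoints: "The primary endpoint is the cumulative rate of toxicity CTCAE ≥ grade 2 in the first 4 months". Under Statistical considerations, the hypothesis to be rejected has photons as comparator: "the null hypothesis of the study is that the toxicity rate in the proton group is greater than or equal to the toxicity rate in" [photon patients]. It is tested at one-sided 0.025. Secondary variables are analysed descriptively, so this is the only formal test.

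Three populations are then defined in the same section:

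- **ITT:** all randomised patients, in the arm to which they were randomised. It is primary for efficacy endpoints and patient characteristics.
- **Per-protocol (PP):** "all patients in the ITT population who received the planned therapy in its entirety" and whose primary-endpoint documentation is complete. It serves as a sensitivity analysis, "used to investigate the robustness of the results from the ITT analysis".
- **Safety:** ITT patients "in whom the planned therapy was started (at least 1 day) belong to the safety population and will be evaluated in the therapy arm" of actual treatment. Of this set the article says: "This is the primary evaluation population for the primary endpoint as well as for all other safety endpoints".

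The article calls the trial open-label (Study design). Photons are given in all participating centres and protons only at the Heidelberg and Marburg ion beam facilities (Target volume delineation and radiotherapy application).

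**The concern.** Grouping by treatment received is a sensible convention for describing harms. Here, however, less toxicity is the benefit that the trial sets out to prove, so the endpoint plays the part that efficacy plays elsewhere. A confirmatory comparison of this kind draws its validity from randomisation. Once patients are regrouped by what they received, the two groups differ by whatever led some of them to switch.

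The design gives switching a route. Allocation is known, and one modality is available at two facilities while the other is available everywhere. A proton-allocated patient may end up on photons because of health, travel or preference, and some of these reasons may be related to toxicity risk. If they are, the as-treated contrast is biased and the nominal error rate is not the actual one. High-risk patients moving to photons would favour protons; low-risk patients moving would hide a benefit.

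The one named sensitivity analysis gives little help. The PP set is described as a check on the ITT analysis, which is not the primary analysis of this endpoint. It also requires completed therapy, so it drops patients who stopped radiotherapy because of toxicity.

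**Working it through.** **Inputs from the Protocol article (Statistical considerations):** photon rate 21%, proton rate 9%, one-sided α = 0.025, power 80%, 138 evaluable per group (276), 15% dropout, 163 per group (326).

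**Inputs assumed, because the documents give none:** the share c of proton-allocated patients who receive photons, and the toxicity risk q of those patients.

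**Step 1. Reproduce the plan's sample size.** Chi-square formula with pooled variance and no continuity correction:

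n = [1.96·√(2·0.15·0.85) + 0.8416·√(0.21·0.79 + 0.09·0.91)]² / 0.12² = 137.8, so 138 per group and 276 in total. Power at 138 is 80.1%. With dropout, 138/0.85 = 162.4, so 163 per group and 326 in total. The plan's figures reproduce; the sample size is not in question.

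**Step 2. Type I error of the as-treated test.** Take the null as true, with rate p = 0.21 in both randomised arms and n = 138 per arm. Let c·n proton-allocated patients with risk q be counted as photon patients.

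- Proton group: size n(1 − c), rate (p − cq)/(1 − c).
- Photon group: size n(1 + c), rate (p + cq)/(1 + c).
- Rejection probability: Φ[(difference − 1.96·SE₀)/SE₁], with SE₀ pooled and SE₁ unpooled; difference is photon minus proton.

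For c = 5%, 6.9 patients move, leaving groups of 131.1 and 144.9, and SE₀ = √[0.21·0.79·(1/131.1 + 1/144.9)] = 0.0491.

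- q = 42%: proton (28.98 − 2.898)/131.1 = 19.9%; photon (28.98 + 2.898)/144.9 = 22.0%. Spurious benefit 2.1 points; (0.0211 − 0.0962)/0.0490 = −1.53; error **6.2%**.
- q = 5%: proton (28.98 − 0.345)/131.1 = 21.8%; photon (28.98 + 0.345)/144.9 = 20.2%. Bias of 1.6 points against protons; (−0.0160 − 0.0962)/0.0492 = −2.28; error **1.1%**.
- q = 21% (switching unrelated to risk), or c = 0: both rates 21%; error **2.5%**.

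The same formula over a wider range (nominal 2.5%):

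| Switching c | q = 5% | q = 21% | q = 42% | q = 60% |
|---|---|---|---|---|
| 2% | 1.8% | 2.5% | 3.7% | 5.0% |
| 5% | 1.1% | 2.5% | 6.2% | 12.1% |
| 10% | 0.5% | 2.5% | 13.4% | 35.6% |

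Analysed by allocated arm, both rates are 21% in every cell, and the error stays at 2.5%.

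**Step 3. Cost of analysing by allocated arm.** If 5% of proton-allocated patients receive photons regardless of risk, the proton-arm rate under the alternative is 0.95·9% + 0.05·21% = 9.6%. Power against 21% is 75.1% with 138 per group and 81.9% if all 163 per group contribute.

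**Step 4. What dropping non-starters can do.** If 5% of the proton arm never start and are left out, with no such loss in the photon arm, the error is about 4.1% when their risk would have been 42% and about 6.2% when it would have been 60%. This is smaller than the effect of moving the same patients, but it is not zero.

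**The case against.** The strongest reply is that the harm is conditional. A reader might infer that the 0.025 error rate is lost as a matter of course. The documents do not support that: they give no switching or non-start rate, and Step 2 shows the error unchanged when switching is absent or unrelated to risk. Nor do they support a fixed direction, since low-risk switchers make the test conservative. This stands, and it is why the size is given as a two-sided range.

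The calculation also uses an unadjusted test, while the plan adjusts for fractionation, subventricular zone involvement and concurrent chemotherapy. Hypofractionation is chosen for age or comorbidities, so adjustment could absorb part of any health-related selection. It cannot be relied on to absorb selection by travel, preference or other aspects of health.

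Two further inferences go too far:

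- That the safety-set definition contradicts itself, because a patient who switched never started the planned therapy and yet is to be regrouped. If planned therapy means study radiotherapy of either kind, the sentence is coherent. It is an ambiguity of wording.
- That an ITT analysis of toxicity is ruled out. The text only makes ITT primary for other endpoints. Tying PP membership to the primary endpoint, and comparing PP with ITT, hints that an ITT analysis of toxicity may exist. It is still not the primary one.

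The PP definition is of a usual kind and serves a sensitivity analysis only, so it is a secondary matter.

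**Conclusion.** The point holds as one of analysis choice. The article states, as a rule and not by omission, that the only confirmatory superiority test is made in patients grouped by treatment received, and it makes no as-randomised analysis of that endpoint primary. Validity then depends on switching being rare or unrelated to toxicity risk, which the design does not guarantee.

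The size is unknown. Under the stated assumptions (21% in both arms, 138 per arm, unadjusted test, 5% switching from protons to photons), the type I error is about 6% with switchers at 42% risk, about 1% with switchers at 5% risk, and near 2.5% otherwise. If few patients switch, the practical effect is small. The case for change is that an analysis by allocated arm removes this dependence on how patients switch at little cost.

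**What to change.** - **Primary analysis of the primary endpoint:** include all randomised patients who started any study radiotherapy, each in the allocated arm. Saying study radiotherapy of either modality also removes the ambiguity in planned therapy.
- **Sensitivity:** an all-randomised analysis where toxicity data exist, to cover the remaining exposure from non-starters shown in Step 4.
- **Supportive:** keep the as-treated safety set for this endpoint and for adverse event tables.
- **PP:** state that it checks the primary analysis just described, and do not exclude patients who stopped radiotherapy because of toxicity.

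The cost is a few sentences in the protocol and analysis plan before database lock. The primary analysis needs no new data. The all-randomised analysis may, because toxicity visits and the evaluation are timed from radiotherapy (Timeline of the study) and patients who never started have no clear window; hence its role as a sensitivity analysis. The sample size of 276 evaluable patients can stand if switching is rare. With 5% unselective proton-to-photon switching, power falls to about 75% at 138 per group.

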### Ethics

The study protocol, patient information and consent form are approved by to the local Ethics Committees (S-204/2019 for Heidelberg, B-F-2021-052 for Stuttgart and positive approval for Marburg/Gießen from 08.05.2020). The procedures set out in this trial protocol are designed to ensure that all persons involved in the trial abide by ICH harmonized tripartite guideline on Good Clinical Practice (ICH-GCP) and the ethical principles described in the applicable version of the Declaration of Helsinki. The trial will be carried out in keeping with local legal and regulatory requirements.

### Data quality assurance and data safety monitoring board

To ensure data quality and consistency, quality control measures are performed regularly. For this purpose, contents are regularly checked by a monitor in 10% of all patients included up to this point (selected at random) as part of quality assurance. Furthermore, an independent Data Safety Monitoring Board (DSMB) will monitor enrollment, reported adverse events, PFS as the primary secondary endpoint, and data quality at least annually. Based on its report, the DSMB will make recommendations to the principal investigator regarding study modification, continuation or termination. The mission of the DSMB will be to ensure the ethical conduct of the study, as well as to protect the safety interests of the patients in the study.

## Discussion

Previous published in-house data has shown that proton beam therapy as a boost concept might offer a dosimetric and clinical benefit in patients with high grade glioma and glioblastoma. This multicenter, prospective, open-label, randomized, two-arm phase III study is the first to investigate whether patients with glioblastoma experience significantly less toxicity when the whole radiotherapy is delivered with proton irradiation compared to classical photon irradiation, and whether this improves patient quality of life without compromising efficacy.

### Trial status

Protocol version 1.2d (12.08.2021). The trial started in April 2021 and is currently recruiting. Length of clinical phase approximately 66 months with planned end of the study in Q3 2025 (last patient in) and Q4 2027(end of follow up).

## Data Availability

The data used in this analysis is from publications available in the public domain.
